#### 2.3.2. Supervision and Social Relationships Module

Theories about criminal conduct emphasize the high relevance of social influences for recidivism (57). Negative social influences have been shown to be a valid predictor for sexual re-offenses and are mentioned as a psychological meaningful risk factor (15). Another risk factor for sexual re-offenses can be described as resistance to rules and supervision (15, 58). Thus, one can hypothesize that effective treatments for convicted ISAC and ICCSEM under CS should support the setup of a social network, which reduces the risk to re-offend. Such a positive social network comprises not only the family, friends, or colleagues but also therapists, SOs and social workers. In the supervision and social relationships module, @myTabu tries to enhance the motivation to build up a (new) positive social network and to reduce resistance to rules and supervision with the help of psycho-educative and cognitive-behavioral techniques; e.g., the correlation between re-offenses and a negative social network are demonstrated and techniques to setup new positive networks and to disassociate from negative social influences are provided. Another important risk factor to re-offend is described as a lack of emotionally intimate relationships with adults (15). Individuals who have sexually offended who are able to maintain a stable partnership with adults showed lower recidivism rates in comparison to individuals who have sexually offended who are not able to maintain stable partnerships to adults (58, 59). Furthermore, Hanson et al. demonstrated a linear correlation between a lack of emotionally intimate relationships with adults and re-offenses (60). In consequence, the risk to re-offend of convicted ISAC and ICCSEM under CS is lower if they maintain emotionally intimate relationships with adults. During the supervision and social relationships module, knowledge about this correlation and support for setting up emotionally intimate relationships with adults is provided. To the best of our knowledge, there exist no studies which have demonstrated the effectiveness of the described content of the supervision module, whether in f2f nor in web-based interventions.

#### 2.3.3. Emotion Management Module

Mann et al. defined lifestyle impulsiveness as low self-control, instability in employment and housing, lack of meaningful daily routines, irresponsible decisions, as well as limited and unrealistic long-term goals (15). Lifestyle impulsiveness is mentioned as an empirically supported risk factor with a broad empirical basis (15, 58). Dysfunctional coping, defined as sexualized coping and external coping styles, is not as well-empirically supported as lifestyle impulsiveness (15). Nevertheless, Knight and Thornton showed that external coping, defined as the tendency to react in a reckless and impulsive manner to stressful and emotional negative events, predicts sexual recidivism (61). @myTabu utilizes Dialectic Behavioral Therapy [DBT; (62)] skills training and Acceptance and Commitment Therapy [ACT; (63)] in order to reduce impulsiveness and to enhance coping abilities during stressful or negative emotional life-events. DBT skills training aims to enhance emotion regulation and distress tolerance by teaching several skills which can be used instead of external or sexualized coping. It has already been shown that DBT is successful in reducing impulsive behavior in forensic populations (64). With regard to other psychiatric disorders, web-based interventions following the principles of DBT have been shown in meta-analyses as effective, especially in reducing stress (65, 66). ACT focuses on the development of a meaningful life by accepting negative inner experiences as they appear and provides additional useful strategies to cope with negative emotions (63). Also ACT has been successfully implemented into offender therapy [e.g., (67)] and shows encouraging results if utilized in web-based interventions for a number of psychiatric disorders (65, 66).

#### 2.3.4. Problem Solving Module

In meta-analyses, poor (social) problem solving is significantly linked to sexual recidivism (15, 68). Social problem solving can be defined “as the self-directed cognitive-behavioral process by which an individual, couple, or group attempts to identify or discover effective solutions for specific problem encountered in everyday living” (69). Within the widely-accepted cognitive model of D'Zurilla and Goldfried, problem solving is seen as two-dimensional: the problem orientation and the problem-solving style. Regarding problem orientation, positive (PPO) and negative problem orientations (NPO) can be observed; PPO facilitates adaptive coping and reduces emotional distress, whereas NPO enhances avoidance behavior and ineffective coping strategies (70). Following the theoretical model, three problem-solving styles can be identified: Rational Problem-Solving (RPS), Impulsive Coping Style (ICS), and Avoidance Style (AS). RPS refers to a systematic and planned application of skills leading to an adaptive solution. ICS is unsystematic and mostly results in implementing the first idea that comes in mind, and AS results in avoiding problems and waiting for external solutions. It has been shown that ISAC displayed higher levels of NPO and lower levels of PPO than the general population. In addition, ISAC tend more to ICS and AS than to RPS (71). Furthermore, there is empirical evidence that poor problem solving of ISAC can be effectively changed by psychological treatment techniques (72, 73). The problem solving module is intended to improve poor problem solving skills by following the well-established Problem-Solving Therapy [PST; (74)]. The focus is on the establishment and training of positive problem orientation and rational problem solving skills.

#### 2.3.5. Offense-Supportive Attitudes Module

Offense-supportive attitudes of ISAC can be summarized as the belief that children are able to build sexually mature relationships, that children are not harmed by sex with adults, and that children consciously provoke sexual behaviors in adults (75–77). These cognitive schemata have to be strictly confined from excuses and attempts of justifying the own specific offenses (15). Helmus et al. demonstrated in a meta-analysis that only offense-supportive attitudes as defined above are a psychological meaningful risk factor in the sense of being predictive for sexual recidivism in ISAC. On the other side, attempts of justifying the own offenses should not be the focus of cognitive treatment of ISAC (78). The offense-supportive attitudes module utilizes cognitive restructuring in order to change offense-supportive attitudes. Cognitive restructuring is the most common and best evaluated technique to change the cognition of ISAC (75). Changing implicit theories, attitudes and beliefs is traditionally difficult, especially in the case of ISAC, since the implicit attitudes are not always harmful for the participant and, in contrast, can serve as a strategy to minimize the harm elicited by own offenses (75). Nevertheless, it has been shown in several studies that cognitive restructuring is effective in changing implicit offense-supportive beliefs and attitudes of ISAC (79, 80). Cognitive restructuring assumes that implicit cognitive theories can be changed by identification and logical re-examination. First, the concept of implicit offense-supportive beliefs is explained and individual distorted beliefs are identified by e.g., re-thinking the offense chain. Second, the identified beliefs are re-framed as offense-supportive and as a hindrance for reaching primary goals. Third, the participant is assisted and motivated to evaluate the identified beliefs with regard to rationality and evidence. By using the socratic dialog technique, the participant is not educated but rather supported to find more adequate, alternative ideas about his beliefs. Fourth, these alternative ideas are excessively compared with the old problematic beliefs in several life situations regarding their evidence (75, 79). To the best of our knowledge, @myTabu utilizes cognitive restructuring for ISAC in a web-based intervention for the first time. Thus, no existing data can be provided with regard to effectiveness of online cognitive restructuring of ISAC. But, several meta-analyses for other psychiatric disorders, e.g., depression, have demonstrated that cognitive restructuring techniques integrated in web-based interventions show medium to large effect sizes (81). It seems to be most important for the effectiveness of this web-based intervention module that it is online-guided by therapists (82).

#### 2.3.6. Sexuality Module

Individuals who have sexually offended have been shown to be more sexually active and interested in sexuality than non-offenders (83). Sexual preoccupation is expressed by sexual thoughts and behavior, which are difficult to control or can not be controlled at all (84). Studies demonstrated that sexual preoccupation is highly correlated with sexual re-offenses (58). Thus, one goal of the sexuality module is to provide basic knowledge about sexuality and to support the reduction of excessive sexual thoughts and activities. Furthermore, an awareness for risky situations that may foster sexual thoughts and behavior is created. Techniques to avoid sexual thoughts and activities are provided in order to reduce sexual preoccupation. Emotional congruence with children is another risk factor targeted in the sexuality module. Convicted ISAC and ICCSEM under CS sometimes have the feeling of being emotionally connected to children. Convicted ISAC and ICCSEM under CS, who identify themselves with children, are getting easier in contact with children (84). Thus, emotional congruence with children is one factor highly associated with re-offenses (58). The sexuality module aims to reduce the emotional congruence with children by psycho-educative techniques. Participants should learn that equal relationships between children and adults are not possible. Furthermore, strategies are provided in order to establish a higher (emotional) distance to children. Sexual interests in (and sexual fantasies about) children is one of the most important risk factors for convicted ISAC and ICCSEM under CS (15, 16, 58, 59) and seems to be a motive for sexual child abuse (85). In order to reduce the risk to re-offend, it may be promising to decrease the sexual interest in children and to spotlight non-deviant sexual interests. It is an ongoing debate in literature, whether sexual interests can change throughout the life-time and there exist not enough empirical evidence to answer this question clearly yet (16). From a clinical point of view, changes of sexual interests are reported as well as highly fixated pedophilic interests, which are not changing over the life-time (16). Sexual interests in children is described as a dynamic risk factor that may or may not change over time. Sexual fantasies about children are illustrated as a risk factor for re-offenses. Cognitive-behavioral techniques are used to influence sexual interest in and, if possible, sexual fantasies about children and to enhance sexual interest in adults. The above described techniques used in the sexuality module have been shown to be effective in f2f treatments (86, 87). Also, at least for young people, some techniques have already been used in web-based interventions (88, 89).

### 2.4. The Placebo Web-Based Intervention (Placebo Condition)

The control condition is a placebo web-based intervention with the same mode, dose, and amount of support and attention by supporting online coaches as in the experimental condition—but the content of the modules is unrelated to the proposed dynamic risk factors. The content of the placebo condition comprises information on healthy living, e.g., healthy nutrition, physical activities, or healthy sleep. The amount of exercises is the same as in the experimental condition but exercises are specifically designed to not induce any sustainable effect.

### 2.5. Outcome Measures

In a 5-years follow-up, officially recorded re-offenses are assessed and analyzed for both treatment arms. In order to control for inter-individual pre-treatment scores and risk-levels, the pre-treatment scores are included as co-variables in the model for the primary endpoints. Following the recommendations of Olver and Wong as well as Olver and Stockdale, treatment change is also measured by risk assessment tools and questionnaires (16, 17).

#### 2.5.1. Primary Outcome Measures

Primary outcome measures comprise officially recorded re-offenses and self-report questionnaires assessing dynamic risk factors.

##### 2.5.1.1. Officially recorded re-offenses

Officially recorded re-offenses in the experimental condition compared to the placebo condition are the first primary outcome. Officially recorded re-offenses are obtained 5 years after last patient out.

##### 2.5.1.2. Index of Desistance (IoD)

The second primary outcome measure is the pre-post intervention difference of the Index of Desistance (IoD) in the experimental condition compared to the placebo condition. The IoD represents the individual risk to re-offend assessed through self-report. This composite measurement reflects improvements with regard to psychological meaningful risk factors, offense behaviors as well as offense-related behaviors that have not been registered or convicted yet. The IoD comprises three self-report instruments, which were developed and are currently evaluated by members of the @myTabu-consortium: (1) The Acute-2007-SR is an online and self-report adaption of the Acute-2007 (90) risk-assessment tool in order to assess treatment induced short-term changes in recidivism risk factors. (2) The Checklist of Treatment Effectiveness (CTE) is developed to assess the differential treatment-induced changes in every individual treatment module. Thus, the CTE assesses the constructs that are targeted by the six modules of the invention. (3) The Checklist of Behavioral Misconduct (CMC) measures offense-related behavior as well as low- and high-level new offenses. Offense-related behavior includes behaviors which are relevant for individuals previously convicted of sexual offenses prior to a new offense (e.g., recidivistic behavior like, e.g., if person convicted of sexual abuse of minors visits a playground or a school). The CMC could be seen as post-treatment deviant behavioral indicators. Please see Supplementary Table 1 for the specific measurement time-points. The IoD will provide the individual risk level to re-offend by summing up the scores of the Acute-2007-SR, CTE, and CMC.

#### 2.5.2. Secondary Outcome Measures

Pre-post difference scores of psychometric questionnaires in the experimental condition compared to the placebo condition are defined as the secondary outcomes. The questionnaires are assessed before and after each corresponding intervention module. This approach allows evaluating each web-based intervention module individually with regard to its targeted risk factors. Supplementary Table 1 gives an overview over all questionnaires and the respective assessment time-points.

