### 2.3. The Web-Based Intervention @myTabu (Experimental Condition)

Psychological treatment in the context of individuals who have sexually offended is most effective when it follows the RNR approach utilizing cognitive-behavioral treatment techniques (9). The RNR approach highlights the fact that effective treatment programs have to concentrate on risk factors, which are changeable (7). Thus, most important for effective treatment frameworks are risk factors with empirical evidence for recidivism and for their changeability by psychological treatments (15). Mann et al. identified empirically supported risk factors for ISAC based on meta-analyses, which build the theoretical basis for the web-based intervention modules. Reviewing treatment techniques, Carter and Mann found that cognitive skills training, cognitive restructuring and experimental techniques are empirically supported (6). Following this rationale, the web-based intervention concentrates only on empirically supported risk factors as well as on treatment methods that have empirical support for the respective risk factors. All web-based intervention modules use already developed therapeutic concepts and are partly based on already established community-based treatment programs (48, 49). These concepts have been adapted for web-based interventions and the specific sample of the trial. Beside of treatment techniques, therapist-client relationship is important: a confrontational therapy style, as proposed in some treatment programs, is obstructive and less effective than an emphatic therapist-client relationship following the principles of motivational interviewing (6). Thus, all web-based intervention modules comprise techniques of motivational interviewing (50) to enhance the motivation of the participants, psycho-educational modules, online training, and tasks in order to learn and practice new ways of thinking and coping. Throughout all modules, the speech is friendly, empathetic, simple, and easy to understand (e.g., no technical terms, examples of everyday life) in order to account for the different cognitive functioning level within the group of convicted ISAC and ICCSEM. Following this rationale, the web-based intervention is conceptualized as a structured intervention which comprises six modules in a fixed order, each targeting different risk factors (see Figure 1 for an overview). The content is provided online by psycho-educational blocks complemented by short videos and images. Eighteen different online exercises (e.g., fill-in-the-gap, multiple choice questions) are used to enable the user to train and to internalize the most important aspects of the psycho-educational blocks. The exercises are provided as self-guided tasks with automatic feedback and as coach-guided tasks, where the feedback is provided by online coaches. The feedback of the online coaches is manualized. Since guided web-based interventions are more effective than pure self-help programs, coach-guided exercises are one possibility to enhance the effectiveness of web-based interventions (37). Virtual participants accompany the participant, talk/narrate about their experiences, and make suggestions from the perspective of someone who is also affected. Furthermore, an in-app messaging system allows the user to communicate in real-time with the online coach as well as the SO. In order to enhance the extrinsic motivation of participants, an automatic reward system is integrated based on a gamification approach. That is, participants receive virtual awards as well as coins for each finished block and filled out questionnaire. The coins can be changed into Euros and when the participant has collected at least 20 Euros, he can request the payout online. The participant can receive a maximum compensation of 120 euros. Finally, an online first aid kit is provided for each user and filled with individual skills prepared by the user itself during the web-based intervention. See Figure 2 for an overview of the intervention concept.

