##### 2.5.2.12. Hypersexual Behavior Inventory-19 (HBI-19)

Sexual preoccupation is assessed by the Hypersexual Behavior Inventory-19 [HBI-19; (110)]. The HBI-19 is a three-factor measure (coping, control, and consequences) developed to assess hypersexual behavior. The instrument consists of 19 items (e.g., “I use sex to forget sorrows of everyday life.”) answered on a scale from 1 (never) to 5 (very often). The maximum score is 95, with higher scores indicating a higher level of sexual preoccupation. The questionnaire was shown to have good reliability (α = 0.90) and validity (110).

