### 2.11. Statistical Analysis

All patients who discontinue from the study are identified and the extent of their participation in the study is reported. If discontinuation is due to clear evidence for recidivism or concrete preparation for or intention to recidivism (assessed by responsible SO or guiding therapist) the subject receives the maximal value for self-reported dynamic risk factors for the remaining measurements (assuming the worst case of a failed treatment). In all other cases of drop-out, the reason is recorded. The efficacy of the web-based intervention based on the first primary outcome measure (IoD) will be analyzed by means of Gaussian linear model for repeated measures (MMRM) with treatment group, time (six time-points; after each web-based intervention module (see Supplementary Table 1); treatment-by-time interaction, and the randomization strata as factors (offense type, type of CS, external treatment in addition to CSaU), and baseline measurements (at clearing up) of the outcome as co-variate. The error terms are assumed to follow a multivariate normal distribution with unstructured co-variance. Least squares mean changes from baseline are reported for the treatment groups with 95% confidence interval (CI) as well as the difference between the least squares treatment group means with 95% CI and *p*-value testing the null hypothesis of no treatment effect. The analysis is performed on the Intention-To-Treat (ITT) population comprising all patients who have completed at least one module. The second primary outcome measure (officially recorded re-offenses) will be analyzed by means of Cox proportional hazard model with treatment group, number of completed modules and the randomization strata (offense type, type of CS, external treatment in addition to CSaU, risk to re-offend at baseline). The effect of each module will additionally be analyzed using the Wilcoxon signed rank test for paired data comparing the pre- and post-module scores, adjusting the *p*-values using the Bonferroni-Holm's method to control the family-wise error rate. Economic analyses will be based on analytic modeling techniques. Data will be derived from the clinical trial (e.g., recidivism rates based on dynamic risk factors), the literature (e.g., tangible benefits), and experimental procedures (e.g., contingent valuation/revealed preference approaches to assess intangible benefits). Results of the analysis will be presented in terms of net benefit (NB) estimates and a benefit-cost ratios. The NB will be calculated as NB = tangible benefits + intangible benefits-intervention costs. The intervention will be considered cost-beneficial relative to the control condition if the NB is positive and the benefit-cost ratio exceeds 1.00 following standard economic decision rules. Since many cost parameters associated with ISAC and ICCSEM occur after the trial period, the cost-benefit of the intervention will be modeled for a 5-years period. Sensitivity analyses will be conducted to examine how the NB will be influenced by variations in model parameters.

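### With one fixed module order, the before/after questionnaires can show only the added change during a module given the modules before it, not the effect of each module individually

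*Protocol article*

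**What the plan says.** Section 2.3 describes the programme as a "structured intervention which comprises six modules in a fixed order, each targeting different risk factors". On the secondary questionnaires, section 2.5.2 states: "The questionnaires are assessed before and after each corresponding intervention module". It defines the outcomes as a contrast with placebo ("Pre-post difference scores of psychometric questionnaires in the experimental condition compared to the placebo condition are defined as the secondary outcomes") and concludes: "This approach allows evaluating each web-based intervention module individually with regard to its targeted risk factors". Section 1.3 makes the effectiveness of the individual modules a stated aim and gives a separate hypothesis for each.

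The module-level test in section 2.11 is described as "using the Wilcoxon signed rank test for paired data comparing the pre- and post-module scores", with Bonferroni-Holm adjustment and no placebo term.

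One instrument covers all targets. In section 2.5.1.2, "the CTE assesses the constructs that are targeted by the six modules", and the CTE is one of three components of the Index of Desistance (IoD). Section 2.11 takes the IoD at clearing up and after each of the six modules, which fits the seven time-points in section 2.6.

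The limitations in section 3.1 mention neither module order nor carry-over.

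**The concern.** For modules 2 to 6, the pre-module score in the experimental arm is taken after one to five active modules. In the placebo arm it is taken after modules unrelated to the risk factors (section 2.4). The placebo comparison removes time, attention and retest effects, because both arms share them. It cannot remove what only the experimental arm has: effects of earlier active modules that are still developing, and changes in how a later module works because of what came before.

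The protocol's own content makes this plausible for some targets:

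- **Emotion management (module 3).** It aims to reduce impulsiveness by "teaching several skills which can be used instead of external or sexualized coping". The scale for the next module, the SPSI-R, includes impulsivity/carelessness and avoidance styles (section 2.5.2.7).
- **Sexuality (module 6).** Its measure of sexual preoccupation also scores coping: "The HBI-19 is a three-factor measure (coping, control, and consequences").
- **Motivation (module 1).** Section 2.3.1 presents motivation as something to address before other needs can change, so it is meant to help the later modules work.

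Section 2.6 and Figure 1 describe weekly sessions, and no washout between modules is mentioned. At stake is what may be concluded about any single module. The primary outcomes are not affected.

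**Working it through.** **1. What the contrast estimates.** Let E(k, pre) and E(k, post) be the experimental-minus-placebo differences on module k's target just before and just after module k. The between-arm difference in change is

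E(k, post) - E(k, pre) = own effect of module k in this sequence + part of earlier modules' effect that emerges in the window (+ any interaction).

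An earlier effect already complete at the pre-module score appears in both terms and cancels. With one order for everyone, no participants take module k without modules 1 to k-1, so the data cannot separate the terms on the right.

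**2. The plan's own figure.** Section 2.10: 582 x (1 - 0.264) = 428.4, hence 428 completers, 214 per arm. Power for d = 0.27, two-sided 5% (sidedness is not stated, but two-sided matches): standard error sqrt(2/214) = 0.0967; 0.27/0.0967 = 2.79; power = Phi(2.79 - 1.96) = 79.8%. The stated 80% reproduces and is not affected by this point.

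**3. Size of the carry-over problem.** The documents give no module-level effect, so these inputs are assumptions:

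- Total effect of earlier modules on the later target: 0.27 SD (borrowed from section 2.10, where it is the overall detectable effect).
- True own effect of module k: zero.
- Pre-post correlation: 0.7.
- 214 per arm, between-arm comparison of change scores, two-sided 5%, before any multiplicity adjustment.

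SD of a change score: sqrt(2 x (1 - 0.7)) = 0.775. Standard error of the between-arm difference: 0.775 x sqrt(2/214) = 0.0749. If a share f of the earlier effect emerges inside the window, the bias is 0.27 x f and the rejection rate is Phi(0.27f/0.0749 - 1.96) + Phi(-0.27f/0.0749 - 1.96).

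| Share f emerging in window | Bias (SD) | False rejection, formula | False rejection, simulation |
|---|---|---|---|
| 0 | 0.00 | 5% | 5% |
| 0.25 | 0.07 | 15% | 15% |
| 0.5 | 0.13 | 44% | 43% |
| 1 | 0.27 | 95% | 94% |

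The f = 0 row confirms step 1: a treated pre-module score does not by itself bias the contrast.

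Sensitivity to the correlation: with 0.5 the change-score SD is 1 and the standard error 0.0967, and f = 0.25 or 0.5 gives 11% or 29%. A multiplicity adjustment lowers these rates but leaves the bias unchanged.

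**4. The test named in section 2.11.** A paired pre-post test within one arm also absorbs changes common to both arms. In simulation with no module effect and the same correlation of 0.7, a shared time trend of 0.10 SD leads the paired Wilcoxon test to reject in 45% of cases, while the between-arm comparison stays at about 5%. The conditional module effect therefore has to be estimated between arms, as section 2.5.2 already implies.

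**The case against.** The strongest reply is that gains made before module k starts belong to the earlier modules, and leaving them out of module k's change is correct attribution. This stands. A reader might infer that the design shrinks each module's effect by whatever share of the total arose earlier; that is not an error of the contrast, and step 3 shows zero bias in that case.

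A reader might also infer that fixed order rules out any module evaluation, or that five of the six modules are biased. The documents do not support either. The added change in this sequence can be estimated against placebo if late effects and interactions are absent. The specific overlap shown in the text is mainly module 3 with the SPSI-R and the HBI-19, plus the enabling role of the motivation module. For the HBI-19, modules 4 and 5 (eight weekly sessions) lie in between, so module 3 effects that appear by then are differenced out.

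Nor can it be said that each questionnaire is given only around its own module. Section 2.5.2 does not say so, and Supplementary Table 1, which holds the time-points, is not shown. The CTE already offers a repeated view of all constructs in both arms.

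Finally, it can be argued that the protocol speaks of a module's effect on its targets within a structured programme, not of a stand-alone effect. That reading is possible, but section 2.5.2 claims individual evaluation without qualification and section 3.1 adds no caveat. No passage plans to keep or drop modules on these results, so that consequence should not be attributed to the protocol.

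**Conclusion.** The point holds in a limited form. For modules 2 to 6, the planned data identify at most the added change during a module given those before it. The statement in section 2.5.2, and the module aim in 1.3 read without qualification, claim more than the fixed order can deliver. Comparing with placebo does not close the gap for late effects or interactions.

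The size cannot be known from the documents. Under the stated assumptions, false rejection for a module with no effect of its own stays at 5% if earlier effects are complete before the window, and rises to about 15% or 43% if a quarter or a half of a 0.27 SD effect emerges within it. These figures illustrate a mechanism and do not predict this trial. The point concerns a stated aim and the secondary outcomes; the sample size and primary comparisons stand apart from it.

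**What to change.** 1. In sections 2.5.2 and 1.3, restate the module-level claim as the effect of module k when given after modules 1 to k-1, estimated as the between-arm difference in change, and bring the module analysis in section 2.11 into line.
2. In section 3.1, name fixed order and carry-over as a limitation.
3. From the CTE collected repeatedly in both arms as part of the IoD, report for each module's construct the between-arm change from clearing up to just before its module, across its module, and from then to the end of module 6. Keep this descriptive. Requiring the step across a module to exceed the earlier drift would label a truly effective module ineffective whenever earlier modules had helped its target more.

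The cost is wording and a little extra analysis, with no new data if the CTE follows the IoD schedule. The price is a more modest claim per module. The CTE construct scores also need defining, since section 2.5.1.2 describes only a summed index and instruments still under evaluation.
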